### Secondary outcomes

2.11

#### Maintaining self-exercise with MODE-II

2.11.1

Maintenance rate of self-exercise program every 3 months during MODE-II (6 and 9 months) will be assessed with phone call assessment. Exercise time using the app will be assessed and compared between the experimental and control groups in MODE-II.

#### Musculoskeletal evaluations

2.11.2

Participants will be assessed for musculoskeletal pain and disability. Physical examinations and radiography for the shoulder, knee, and lumbar spine will be conducted at baseline and at close-out. Musculoskeletal pain and disability will be assessed using the SPADI,^[6]^ WOMAC,^[7]^ and ODI.^[8]^ Physical evaluations will be conducted, including range of motion and tenderness evaluations and the Neer test for the shoulder joints; range of motion and tenderness evaluations for the knee joints; and the straight leg raising test and foot dorsum sensory, long toe extensor weakness, and tenderness evaluations for the lumbar spine. Radiography for both knees (Rosenberg view), lumbar spine (anteroposterior and lateral view), and both hands (posteroanterior view) will be conducted.

The SPADI was developed for the assessment of patients with shoulder pain.^[6]^ The SPADI was translated into Korean, and its validity and reliability were assessed.^[9]^ The SPADI is a self-administered questionnaire consisting of 13 items divided into 2 subscales: a 5-item subscale that measures pain (pain symptoms) and an 8-item subscale that measures disability (physical function). The participant is instructed to place a mark on the numerical rating scale (NRS) ranging from 0 (best) to 10 (worst) for each item that best represented their shoulder problem. Each subscale is summed and transformed to a score out of 100, with a higher score indicating greater impairment or disability.

The WOMAC was developed specifically to measure the outcomes of patients with lower extremity arthritis. The WOMAC was translated into Korean, and its validity and reliability were assessed.^[7]^ The WOMAC is a self-administered questionnaire and contains 24 items categorized in 3 subscales: pain, stiffness, and physical function. Each item is scored as 5-point Likert scale format: none (0), mild (1), moderate (2), severe (3), and extreme (4). Scores for each subscale were determined by summing the component item scores for each subscale (possible score range, Pain: 0–20, Stiffness: 0–8, Physical function: 0–68). The final total aggregated scores (possible score range: 0–96) were determined by summing the scores for each subscale. ODI is a self-administered 10-item questionnaire covering intensity of pain and disability in standing, personal care, sleeping, lifting, sex life, walking, social life, sitting, or traveling. ODI was translated into Korean, and its validity and reliability were assessed.^[10]^ Scores for each item range from 0 (no pain or disability) to 5 (severe pain or dis- ability). Scores are reported as percentages according to the following formula: total score (0–50)/maximum score (50) × 100.^[8]^

#### Muscular strength

2.11.3

The muscular strength of the trunk extension and hand grip will be evaluated during the baseline and close-out assessments.

Isometric trunk extensor strength will be measured in the sitting posture using a hand-held dynamometer (Power Track II Commander Muscle Tester, JTECH Medical, UT) positioned at the inferior angle of the scapula (at the level of T7). A custom-made chair designed by authors will be used, which ensures that participants’ feet are off the floor to remove the influence of the lower limbs.^[11]^

Hand grip strength will be assessed by trained technicians using a hydraulic hand dynamometer (SH5001, Saehand Corp., Masan, Korea). Participants will be seated comfortably on a chair without armrests, and the shoulder will be adducted and neutrally rotated, the elbow will be held at 90° of flexion, and the forearm and wrist will be maintained in a neutral position.

#### Balance ability

2.11.4

The Timed Up & Go (TUG) is a test of balance. Participants will be required to sit on a chair, stand and walk a 3-m course at a comfortable speed, walk back to the chair and sit again. The time from standing up to sitting down again will be measured, with prolonged time associated with increased falling risk.^[12]^

The Berg Balance Scale (BBS) is an evaluation tool designed to measure balance and is composed of 14 items.^[13]^ Each item is made up of 5-point scale ranging from 0 to 4, with 0 indicating the lowest level of function and 4 the highest level of function. The BBS was translated into Korean, and its reliability was assessed.^[14]^ The total possible score on the BBS is 56, which indicates excellent balance. A score of <45 indicates individuals that have a greater risk of falling.^[15]^

#### Muscle mass and fat mass

2.11.5

Muscle mass and fat mass will be measured with a body composition analyser (Inbody370S, Seoul, Korea) using direct segmental multi-frequency bioelectrical impedance analysis at baseline and close-out.

#### Depression

2.11.6

The Patient Health Questionnaire-9 (PHQ-9) is a self-administered questionnaire and is a valuable screening instrument for detecting major depressive disorders.^[16]^ PHQ-9 was translated into Korean, and its validity and reliability were assessed.^[17]^ PHQ-9 includes 9 items pertaining to the Diagnostic and Statistical Manual of Mental Disorders-IV criteria for major depressive disorder: anhedonia; depressed mood; trouble sleeping; feeling tired; change in appetite; guilt, self-blame, or worthlessness; trouble concentrating; feeling slowed down or restless; and thoughts of being better off dead or hurting oneself.^[16]^ Each item is rated on a 4-point scale from 0 to 3 (0—never; 1—several days; 2—more than half the time; and 3—nearly every day) during the 2 weeks before and including the day of survey completion. The overall scores range from 0 to 27. A cutoff score of 5 is associated with a sensitivity of 80% and specificity of 78% for depressive disorders.^[17]^

### Criteria for discontinuation

2.12

Voluntary withdrawal of consent from the trial.

### Harms and benefits

2.13

Each exercise is commonly used. All exercises and using the application are not expected to be inconvenient or unsafe to the user. If there is a condition that requires the termination of the research due to medical or subjective reasons, the corresponding patient will be withdrawn from the study. Reasons for discontinuation will be recorded.

### Data and Safety Monitoring Plan

2.14

Each participant's identification number and baseline data will be contained in CRFs. Outcome data will be recorded in the CRF by 2 independent trained research assistants with a double-entry method. Data on assessments will be monitored. Only those who have been previously authorized by the principal investigator can access the data. The data monitoring committee will check the state of recruitment, assessed data, and adverse events, and will guide the research team regarding any needed steps.

### Sample size calculation

2.15

We assumed that the exercise completion rate with 3-month self-exercise using the smartphone app would be 60%; we expected that the completion rate with 3-month self-exercise by providing physical education data (booklets) would be 40%. With these assumptions, we estimated that we would need to enroll 200 participants for MODE phase I with an alpha level of 0.05 and a beta level of 0.20. With 20% of phase I subjects expected to drop out, 160 subjects would be needed for MODE phase II.

### Statistical analysis

2.16

Statistical analyses will be performed using SPSS version 24 (IBM, Armonk, NY). We will use the independent samples *t* test (Student *t* test) to evaluate quantitative data with a normal distribution and the Mann-Whitney *U* test to evaluate data without a normal distribution. The Pearson *χ*^2^ test or Fisher exact test will be used to analyze qualitative comparative data. *P* values of <.05 will be considered significant.

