### Study design

2.1

This study is planned as 2 randomized control trials. The phase I and II trials of the MObile Delivered self-Exercise (MODE) study will be randomized, prospective, single-blind (evaluator), and include active comparator controlled trials to test the effect of an app-delivered self-exercise program on the facilitation of self-exercise, musculoskeletal pain, and health behavior in female farmers aged 41 to 70 years. This study has been approved and conforms to the Declaration of Helsinki. This study was designed according to the CONsolidated Standards Of Reporting Trials (CONSORT) statement^[4]^ and is reported according to the Standard Protocol Items: Recommendations for Interventional Trials (SPIRIT) statement.^[5]^ The schedule of trial enrolment and assessments is shown in Table 1. The trial flow chart is shown in Figure 1.

**Table 1 T1:** The schedule of trial enrolment and assessments.

	Study Period								
Assessment	Enrolment	Allocation	MODE I		MODE II				Close-out
Time point	-t_1_	0	t_1_	t_2_	t_3_	t_4_	t_5_	t_5_	t_6_
Enrolment:									
Eligibility screen	X								
Informed consent	X								
Allocation		X			X				
Interventions:									
Tool usage education			X		X				
App-delivered exercise group				X		X	X	X	
Booklet-delivered exercise group				X					
Assessment:									
Demographics		X							X
Agricultural information		X							X
Medical history		X							
Current medication		X							X
Smartphone usability		X							
Participation in self-exercise				X		X	X	X	
Satisfaction with self-exercise				X		X	X	X	
Depression (PHQ-9)		X		X					X
Shoulder disability (SPADI)		X		X					X
Hip and knee disability (WOMAC)		X		X					X
Back disability (ODI)		X		X					X
Vital sign		X							X
Anthropometric measurement		X		X					X
Bioimpedance analysis		X		X					X
x-Ray		X							X
Bone density DEXA		X							X
Trunk extension strength		X							X
Musculoskeletal physical examination		X							X
Hand grip strength		X							X
Balance test (TUG and BBS)		X							X
Pulmonary function test		X							X
Blood chemistry		X							X

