### Assessment

2.8

The primary and secondary outcomes will be assessed at baseline, 3 months, 6 months, 9 months, 12 months, and postintervention (Table 1). All participants will be requested to complete follow-up assessments, except for those who withdraw or are withdrawn from the study. Those who withdraw will be asked to identify reasons for withdrawal. After the completion of the MODE-II exercise, all subjects will undergo close-out assessment.

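### The continuous secondary outcomes are compared by two-sample t or Mann-Whitney tests with no baseline adjustment named, which loses precision although a baseline value is collected for each

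*Protocol article*

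**What the plan says.** Section 2.16 assigns the independent-samples t test "to evaluate quantitative data with a normal distribution and the Mann-Whitney" U "test to evaluate data without a normal distribution". The threshold is that P "values of <.05 will be considered significant"; sidedness is not stated. The section names no covariate, regression model or change score, and it does not distinguish outcomes, time points or phases.

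The measurements are scheduled as follows.

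- **Pain, disability and depression.** Section 2.11.2 states: "Musculoskeletal pain and disability will be assessed using the SPADI", together with WOMAC and ODI. The Table 1 rows beginning "Shoulder disability (SPADI" and "Depression (PHQ-9", and those for WOMAC and ODI, are marked at allocation, at the second MODE-I time point (read here as 3 months) and at close-out.
- **Strength.** Section 2.11.3 states: "The muscular strength of the trunk extension and hand grip will be evaluated during the baseline and close-out assessments". Table 1 agrees.
- **Balance (TUG, BBS).** Table 1 marks allocation and close-out only.
- **Body composition.** Table 1 marks allocation, 3 months and close-out for bioimpedance, but section 2.11.5 gives only baseline and close-out.

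Section 2.8 is broader: "The primary and secondary outcomes will be assessed at baseline, 3 months, 6 months, 9 months, 12 months, and postintervention". It refers to Table 1, which is narrower, and Table 1 is followed here.

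**The concern.** Each continuous secondary score has a value taken before the MODE-I randomisation, and some also have one taken at 3 months, before MODE-II. No analysis stated in section 2.16 adjusts for either. When an earlier value predicts the later one, a comparison that leaves it out has a larger standard error than the data require.

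The protocol itself treats baseline status as important. Section 2.7.1.1 uses SPADI, WOMAC and ODI to grade each body region and sets the exercise level from that status. Section 2.6 describes block randomisation to equalise numbers and names no stratification by severity. The sample size in section 2.15 rests on completion rates alone, so nothing else in the plan secures precision for these scores.

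A second weakness is that the choice between a mean-based and a rank-based test depends on how the data turn out to be distributed. The quantity compared is therefore not settled in advance and could differ between time points on the same scale. The rank test alone gives no mean difference in scale points.

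**Working it through.** **The plan's own figure.** The only sample size in the article is for the binary completion outcome: 60% against 40%, alpha 0.05, beta 0.20 (section 2.15). With a two-sided test and no continuity correction,

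n per arm = [1.960 × √(2 × 0.5 × 0.5) + 0.842 × √(0.6 × 0.4 + 0.4 × 0.6)]² / 0.2² ≈ 97,

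or 194 in total, within 3% of the stated 200. The figure reproduces, but it says nothing about the continuous scores, for which no power is stated.

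**Inputs for this point.**
- 100 per arm in MODE-I (200 women, 1:1).
- 80 per arm in MODE-II (200 × 0.8 = 160, 1:1).
- Correlation rho between the pre-randomisation and follow-up values: not in the article; assumed 0.3 to 0.7.
- Equal variance at both times, two-sided 5% test.

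**Variance of the estimated difference, with follow-up only set to 1.**
- Follow-up only: 1
- Unadjusted change: 2(1 − rho)
- ANCOVA: 1 − rho²
- ANCOVA relative to change: (1 − rho²) / [2(1 − rho)] = (1 + rho)/2

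| rho | ANCOVA v follow-up only | Variance cut | ANCOVA v change | Variance cut |
|---|---|---|---|---|
| 0.3 | 0.91 | 9% | 0.65 | 35% |
| 0.5 | 0.75 | 25% | 0.75 | 25% |
| 0.7 | 0.51 | 49% | 0.85 | 15% |

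**Equivalent sample size.** 100 per arm with ANCOVA equals 100/(1 − rho²) per arm in a follow-up-only comparison: about 110, 133 and 196 at rho 0.3, 0.5 and 0.7.

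**Detectable difference at 80% power.** Follow-up only: (1.960 + 0.842) × √(2/n) = 0.396 SD at 100 per arm and 0.443 SD at 80 per arm. ANCOVA multiplies this by √(1 − rho²).

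| rho | 100 per arm | 80 per arm |
|---|---|---|
| follow-up only | 0.396 SD | 0.443 SD |
| ANCOVA, 0.3 | 0.378 SD | 0.423 SD |
| ANCOVA, 0.5 | 0.343 SD | 0.384 SD |
| ANCOVA, 0.7 | 0.283 SD | 0.316 SD |

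**Power at the effect where the follow-up-only test has 80%.** At rho 0.3, 0.5 and 0.7, ANCOVA has 83.6%, 89.9% and 97.5%; an unadjusted change score has 65.8%, 80.0% and 95.1%. ANCOVA is ahead of both at every value.

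**Does the switch between tests inflate type I error?** This was simulated with skewed (gamma) data, 80 per arm, no true difference and 5,000 runs for each of two shapes. A Shapiro-Wilk test was assumed as the trigger, since the article names none. The rejection rate was about 4.6% both times. No inflation was shown.

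**The case against.** **The baseline may not be discarded.** Section 2.16 does not say what quantity enters the test, and a t test on change from baseline fits its wording. A reader might infer that the baseline values are thrown away; the text does not establish that. What stands is narrower: no adjustment is named, and the choice between follow-up and change is left open. The gain from ANCOVA survives under either reading.

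**The paragraph is generic and the article is condensed.** A covariate list could sit in an unseen analysis plan. That limits the point but does not remove it, because the article does state the test family for quantitative data. Equally, no formal normality test is named; only the dependence on the distribution is stated.

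**This is efficiency, not validity.** Correct. Under 1:1 randomisation the unadjusted difference is unbiased, and its standard error already allows for chance imbalance. A reader might infer bias or a raised false-positive rate. Randomisation answers the first, and the simulation gave no sign of the second.

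**The main conclusions do not depend on it.** Also correct. The hypotheses at the end of the Introduction, the primary outcome in section 2.10 and the sample size in section 2.15 all concern completion, which is binary and has no baseline value.

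**The correlation may be low.** Strength and balance are measured only at month 0 and close-out, about a year apart, so a low value cannot be excluded there. The range therefore starts at 0.3, where the gain over follow-up only is a modest 9%.

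**Floor effects.** Sections 2.4 and 2.5 set no pain threshold for entry. That could mean widely spread scores or many near zero, and the article does not settle which. With many scores near the floor a rank test is defensible, which is a reason to keep one as a sensitivity analysis.

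**Conclusion.** The point holds as a loss of precision in the continuous secondary outcomes. ANCOVA would cut variance by 9% to 49% against a follow-up-only comparison and by 15% to 35% against an unadjusted change score. Both ranges rest on an assumed correlation of 0.3 to 0.7 and on similar variance at both times. The direction does not depend on the exact correlation; the size does.

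The documents do not support saying that the planned comparison is biased, that its type I error is inflated, that the baseline is certainly ignored, or that the completion outcome is affected. The change is worth making because it improves a method the article already states, using data already scheduled.

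**What to change.** In section 2.16, replace the t/Mann-Whitney rule for the continuous secondary scores with a linear model containing randomised arm and the pre-randomisation value of the same score. Report the adjusted mean difference with a 95% CI. If residuals are skewed, use robust or bootstrap standard errors instead of changing the test; a rank test may stay as a sensitivity analysis.

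- **MODE-I (3 months).** Apply the model only to scores measured then: SPADI, WOMAC, ODI and PHQ-9, adjusting for the month-0 value. Add body composition only if the 3-month measurement in Table 1 is confirmed against section 2.11.5. In Table 1 strength and balance have no 3-month value, so they have no MODE-I comparison.
- **MODE-II (close-out).** Adjust for the 3-month value where one exists and for the month-0 value otherwise (strength and balance). This takes MODE-II allocation to follow the 3-month assessment, as section 2.7.2.1 and Table 1 have it. Section 2.6 ties that allocation to completing 9 months of exercise, and its wording needs to be reconciled with them.

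The cost is a change of statistical wording. SPSS, already named, fits the model, and no further measurements are required. The wording should be fixed before any comparative results are seen.

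### The MODE-I primary test is valid, but it leaves unused the baseline values Table 1 already collects; one pre-specified adjusted analysis would be a modest efficiency gain needing no extra participants

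*Protocol article*

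**What the plan says.** All references are to the protocol article.

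- **Primary outcome (2.10).** Completion of the self-exercise programme, obtained by a yes/no telephone question at 3 months for MODE-I.
- **Test (2.16).** Only two-group tests are named. For categorical data the Pearson chi-square "test or Fisher exact test will be used to analyze qualitative comparative data". No regression model or covariate appears.
- **Randomisation (2.6).** Computer-generated blocks, 1:1. The article names no stratification factor.
- **Baseline data (Table 1).** The row "Smartphone usability" is marked once, at time point 0. Demographics, SPADI, WOMAC and ODI are also marked there, before the tool education at t1.
- **Sample size (2.15).** The app "completion rate with 3-month self-exercise using the smartphone app would be 60" per cent and the booklet "completion rate with 3-month self-exercise by providing physical education data (booklets) would be 40" per cent, "with an alpha level of 0.05 and a beta level of 0.20", so that "we would need to enroll 200 participants for MODE phase I". The section continues: "With 20% of phase I subjects expected to drop out, 160 subjects would be needed for MODE phase II".

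**The concern.** Women aged 41 to 70 are asked to follow a home programme from either an app or a booklet. Age, ease with a smartphone and the degree of shoulder, knee and back disability could each influence who completes it. All are measured before treatment, and the stated primary comparison uses none of them. Smartphone usability is not used in any analysis that the article describes.

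A covariate that predicts a binary outcome can sharpen the estimated treatment effect without changing the question, provided that the result is reported as a standardised (marginal) risk difference. The planned 200 is only 6 above the 194 that the calculation requires, so some unused precision may be worth having.

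**Working it through.** **Inputs.** From 2.15: p1 = 0.60, p0 = 0.40, alpha 0.05, power 0.80, 200 women (100 per arm). Sidedness is not stated. Two-sided is assumed because it reproduces the plan; one-sided would give 154.

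**1. The plan's own figure.** With mean proportion 0.5:

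n per arm = [1.960·√(2·0.5·0.5) + 0.842·√(0.6·0.4 + 0.4·0.6)]² / 0.20² = (1.386 + 0.583)² / 0.04 = 96.9

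This rounds up to 97 per arm, or 194 in total, so the stated 200 is reproduced with a small margin.

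**2. Power of the unadjusted test.** With m per arm, power = Φ[(0.20 − 1.960·√(0.5/m)) / √(0.48/m)].

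- m = 100: (0.20 − 0.1386)/0.0693 = 0.886, power 81.2%.
- m = 80: (0.20 − 0.1549)/0.0775 = 0.582, power 72.0%.

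Exact binomial power is 82.6% and 71.5% for the chi-square, and 78.7% and 65.8% for Fisher. The second case applies only if 40 of the 200 women have no 3-month outcome.

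**3. Adjustment by formula.** Let R² be the share of outcome variance that the covariates explain within arms. The document gives no value, so it is varied. Multiplying both variances in step 2 by (1 − R²) gives:

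| Assumed R² | 200 analysed | 160 analysed |
|---|---|---|
| 0 | 81.2% | 72.0% |
| 0.05 | 83.2% | 74.2% |
| 0.10 | 85.1% | 76.5% |
| 0.15 | 87.1% | 78.8% |

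**4. Adjustment by simulation.** There were 4,000 trials per setting, with three baseline covariates predicting equally in both arms. The uncorrected chi-square was compared with the test of arm in a logistic model.

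| R² | 200: chi-square → adjusted | 160: chi-square → adjusted |
|---|---|---|
| 0 | 83.3 → 82.2% | 71.4 → 71.8% |
| 0.037 | 81.9 → 81.7% | 71.1 → 73.0% |
| 0.095 | 82.8 → 84.3% | 70.8 → 75.2% |
| 0.149 | 82.4 → 85.9% | 71.6 → 78.1% |

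A separate simulation of 3,000 trials per setting, for R² from 0.04 to 0.16, gave gains of about 0 to 4 points with 200 and 2 to 7 points with 160. At 200 the simulated gains are smaller than the formula's, partly because the exact chi-square power there (82.6%) already exceeds the normal approximation (81.2%).

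**5. Covariates that matter in the app arm only** (6,000 trials per setting).

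- Odds ratio 2 per SD: 83.2 → 82.3% with 200, and 70.7 → 72.5% with 160.
- Odds ratio 3 per SD: 82.6 → 82.8% with 200, and 71.9 → 74.0% with 160.

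The separate simulation gave about 1 point with 200 and 2 to 3 points with 160. The gain is therefore between nil and about 1 point with 200, and about 2 to 3 points with 160.

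**6. Type I error of the adjusted test.** It was 4.9 to 5.5% in 6,000 null trials per setting, and about 5 to 6% in the separate simulation.

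**Limit of the check.** Steps 4 to 6 test the arm coefficient with three covariates. The model under fix has five and is judged on the standardised risk difference, so these figures are a guide to its performance and not an exact forecast.

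**The case against.** The strongest objection is that nothing here is wrong. A chi-square test is valid for a 1:1 randomised yes/no outcome, it matches the basis of the sample size, and with 200 analysed it meets the stated power. Covariates are often left to a fuller document that is not shown, and a condensed article's silence on stratification does not prove that there is none. The gain rests on an R² that the document does not supply. Smartphone usability may predict app use but not booklet use, and section 2.4 admits only smartphone users, which narrows its range. Most of this stands, and it limits the point to one of efficiency. The point survives because section 2.16 does more than stay silent: it names the test, and that test is unadjusted.

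Three stronger readings are tempting, and the document does not support them.

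- **That chance imbalance in smartphone skill biases the comparison.** Under randomisation, such imbalance is already part of the variability that the test allows for. The type I error is unaffected.
- **That the primary test has only about 72% power.** This needs 40 women missing from the 3-month analysis. Section 2.15 uses the 20% dropout only to derive the MODE-II number and does not say how many 3-month outcomes will be missing.
- **That baseline risk level can simply be added to the model.** Section 2.7.1.1 speaks of three levels, then of mild and severe groups, then of high and moderate risk, while Table 3 lists mild and high. The variable is not defined well enough to serve as a covariate, and these passages must be reconciled.

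**Conclusion.** The point holds as an optional but worthwhile improvement to a stated method. The unadjusted test is valid and has about 81% power with 200 analysed. Pre-specified adjustment is worth about 0 to 4 points of power with 200 and about 2 to 7 points with 160, if the covariates explain 4 to 16% of the outcome variance in both arms. It is worth at most about 1 point with 200 and 2 to 3 points with 160 if they act in the app arm alone. With 200 analysed and R² near 0.04 or below, there is no useful gain. With uninformative covariates the simulated loss was about 1 point with 200 and none with 160, which is not material.

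These sizes depend on the assumed R², on a two-sided 5% test and on the plan's 60% and 40%. Adjustment does not make up for leaving the MODE-I sample size uninflated for dropout; that is a separate matter.

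**What to change.** In section 2.16, before any outcome data are seen, name one adjusted primary analysis for MODE-I:

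- a logistic regression of 3-month completion on arm, age, baseline smartphone usability, and baseline SPADI, WOMAC and ODI scores, all taken at time point 0;
- the standardised risk difference with its 95% CI as the quantity that decides the comparison, which keeps the marginal question on which the sample size was based;
- the unadjusted chi-square as a supportive analysis.

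Use the three scores in place of risk level. State how smartphone usability is scored, since Table 1 gives only a row label, and how each covariate enters the model. Separately, reconcile the risk coding between section 2.7.1.1 and Table 3.

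The cost is a short paragraph and the covariate definitions. No new measurements or participants are needed.
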